# Safety and Efficacy of Bis-Glyceryl Ascorbate (Amitose DGA) to Prevent Hand-Foot Skin Reaction in Patients With Renal Cell Carcinoma Receiving Sunitinib Therapy: Protocol for a Phase I/II, Uncontrolled, Single-Arm, Open-Label Trial

**DOI:** 10.2196/14636

**Published:** 2019-08-12

**Keywords:** hand-foot skin reactions, renal cell carcinoma, tyrosine kinase inhibitors, ascorbic acid derivative

## Abstract

**Background:**

Hand-foot skin reaction (HFSR) is a serious side effect induced by multiple-tyrosine kinase inhibitors (TKIs). HFSR can cause treatment interruption or decreased dosing. HFSR also markedly decreases quality of life and is associated with the therapeutic efficacy of multiple-TKIs. Therefore, the management and prevention of HFSR is an important issue; however, an effective method for its prevention has not been established. Specific ascorbic acid derivatives can reverse multiple-TKI-induced keratinocyte growth and pathological changes in vitro.

**Objective:**

This study was designed to evaluate the safety of bis-glyceryl ascorbate (Amitose DGA), a novel, hydrosoluble, and moisturizing ascorbic acid derivative, in patients with renal cell carcinoma (RCC) receiving sunitinib therapy. This study was also designed to evaluate Amitose DGA’s preventive efficacy for sunitinib-induced HFSR.

**Methods:**

This is a Phase I/II, single-center, uncontrolled, single-arm, open-label trial. We will recruit a total of 30 patients with RCC receiving sunitinib therapy, with a 2-week-on and 1-week-off schedule. The participants will apply Amitose DGA-containing cream over both palmar and plantar surfaces within two treatment cycles (ie, 6 weeks) of sunitinib in combination with a general moisturizing agent, in addition to standard-of-care processes. Safety assessments will include dermatological abnormalities, clinical laboratory tests, and incidence of adverse events. Efficacy assessments will include development of HFSR and therapeutic outcomes associated with sunitinib.

**Results:**

Recruitment to the study began in August 2017 and is ongoing in Japan. To date, 21 subjects have been recruited. Study completion is expected in 2021.

**Conclusions:**

This is the first clinical study of Amitose DGA-containing cream in patients with RCC who are receiving sunitinib therapy. The single-center, single-arm, open-label design was selected to maximize subject exposure and increase the likelihood of achieving our study endpoints. The results will provide valuable and preliminary evidence of the effects of Amitose DGA-containing cream on HFSR.

**Trial Registration:**

UMIN Clinical Trials Registry UMIN000027209; https://upload.umin.ac.jp/cgi-open-bin/ctr /ctr_view.cgi?recptno=R000031174

**International Registered Report Identifier (IRRID):**

DERR1-10.2196/14636

## Introduction

### Background

In recent years, several types of novel multiple-tyrosine kinase inhibitors (TKIs) against renal cell carcinoma (RCC) have been developed and applied in clinical practice settings [1]. Sunitinib, a multiple-TKI, is an especially important first-line therapy option for patients with metastatic RCC and is the most commonly used agent in clinical settings [2,3]. However, multiple-TKIs can cause serious side effects, which might cause treatment interruption or decrease of dose [4,5]. Hand-foot skin reaction (HFSR) is one such side effect. HFSR is a common and characteristic adverse reaction to multiple-TKIs [6,7] and develops as hyperkeratosis and redness on the palmar and plantar surfaces [7-9]. These side effects can cause walking difficulties and depressed holding and gripping function by the hands, potentially decreasing quality of life; in addition, there is a well-known association between development of HFSR and the therapeutic efficacy of multiple-TKIs [10,11]. Therefore, the management and effective prevention of HFSR has the potential to improve quality of life and the therapeutic outcomes of multiple-TKI treatments [10,12]. Although multiple-TKI-induced HFSR is recognized as a serious problem in clinical practice, effective methods for prevention have not been established.

We recently reported on ascorbyl-2-phosphate magnesium (P-VC-Mg), a highly permeable ascorbic acid derivative; we found that it could relieve multiple-TKI-induced keratinocyte growth inhibition and pathological changes in human keratinocyte cells in a 3D skin model, mediating signal transducer and activator of transcription 3 phosphorylation levels [13,14]. This report suggested that specific ascorbic acid derivatives can prevent multiple-TKI-induced HFSR. Because ascorbic acid derivatives are widely used within cosmetic preparations, it may be possible to establish additional safety parameters.

Bis-glyceryl ascorbate (Amitose DGA) is a novel hydrosoluble and moisturizing ascorbic acid derivative produced by binding ascorbic acid to glycerin. It is easily formulated as an emulsion and gel cosmetic because it is nonionic and has higher permeability and stability compared to other ascorbic acid derivatives. Our preliminary investigation used various ascorbic acid derivatives for keratinocyte growth inhibition with sunitinib. Amitose DGA showed the highest preventive effects among all the products examined, including P-VC-Mg. This effect was attributable to higher cellular translocation and environmental stability of Amitose DGA. There are various reports about the anti-inflammatory effects of ascorbic acid derivatives in healthy or diseased skin and keratinocytes [15-17]; however, its effects on HFSR induced by anticancer agents have not been reported. In spite of this, we consider Amitose DGA to be a strong candidate for HFSR prophylaxis.

### Study Objectives

The primary objectives of this study are to evaluate the dermatological safety of Amitose DGA in patients with RCC who are receiving sunitinib therapy (Phase I) and to determine its prophylaxis efficacy in sunitinib-induced HFSR (Phase II). The secondary objectives are as follows:

Evaluate hematological abnormality of Amitose DGA-containing creamEvaluate the effects of Amitose DGA-containing cream on severe sunitinib-induced HFSREvaluate the effects of Amitose DGA-containing cream on therapeutic outcomes related to sunitinib

## Methods

### Study Design

This study was designed to verify whether Amitose DGA safely and effectively prevents multiple-TKI-induced HFSR. This is an ongoing Phase I/II, single-center, uncontrolled, single-arm, open-label clinical trial to evaluate the safety and efficacy of Amitose DGA-containing cream as a prophylaxis for sunitinib-induced HFSR. Figure 1 summarizes the study design.

### Study Location and Population

Subjects are being recruited from Kobe University Hospital, Kobe, Japan. The population of this study includes patients with RCC who are receiving sunitinib therapy at the hospital.

### Ethics Approval and Consent to Participate

This study was approved by the Ethics Committee at Kobe University Hospital (approval number: 290015) on August 22, 2017. Each participant will sign an informed consent form, which is worded in lay terms, following a comprehensive explanation of study procedures by a research collaborator; study-related risks and benefits will also be explained before participating in the study. To maximize the opportunity for free and informed consent, while respecting privacy and confidentiality, the informed consent process will take place privately. Potential participants will not be invited to join the study if the clinical research coordinator is not able to adequately explain the study and obtain informed consent. The study will be conducted in compliance with the protocol; regulatory requirements; Ethical Guidelines for Medical and Health Research Involving Human Subjects published by the Japanese Ministry of Health, Labour and Welfare; and the ethical principles of the latest version of the Declaration of Helsinki. Each substantial protocol amendment will receive approval by the Ethics Committee prior to implementation.

**Figure 1 figure1:**
[figure not shown]
Flowchart of the study design.

### Inclusion and Exclusion Criteria

We will include individuals capable of providing informed consent, aged 20 years or older, with histologically diagnosed RCC, receiving sunitinib therapy, with or without prior molecular targeted therapy, and before or after nephrectomy. All patients have an Eastern Cooperative Oncology Group Performance Status of 0-2 and are expected to survive for more than 12 weeks at screening. Finally, all the included patients will be determined to exhibit higher compliance for applying the investigational cream, attending clinical visits, undergoing laboratory tests, and keeping a personal dairy based on the study protocol. We will exclude patients with dermatological abnormalities of the palmar or plantar surfaces; those who use topical medications on the palmar or plantar surfaces, except for heparinoid or urea-containing cream; those who are unable to apply the heparinoid or urea-containing cream to the palmar or plantar surfaces; those with grade 1 or higher HFSR based on the Common Terminology Criteria for Adverse Events (CTCAE), version 4.0, at the start of sunitinib therapy; and those with active infections requiring treatment. We will also exclude patients with severe liver injury (ie, alanine aminotransferase ≥5 × upper limit of normal or 2 × individual baseline value); severe kidney injury (ie, serum creatinine level ≥2 × individual baseline value); and other patients who are determined to be inappropriate for study participation by the principal investigator.

### Intervention

The participants will apply three fingertip units of Amitose DGA-containing cream all over both the palmar and plantar surfaces more than three times a day, within two treatment cycles (ie, 6 weeks) of sunitinib. They will also apply heparinoid or urea-containing cream as a standard preventive treatment for HFSR following application of the investigational cream. The participants will be instructed to apply the investigational cream to moist skin, such as when washing their hands or feet, during face washing, or after bathing. The participants will keep a personal diary to record the frequency of application of Amitose DGA-containing cream.

### Study Outcomes

#### Primary Outcomes

The primary outcome of Phase I is development of dermatological abnormalities on the palmar or plantar surfaces, such as bullous dermatitis, dry skin, erythroderma, pruritus, purpura, rash maculopapular, skin hyperpigmentation, and skin hypopigmentation, within two cycles (ie, 6 weeks) of sunitinib therapy. The primary outcome of Phase II is development of grade 1 or higher HFSR within 6 weeks after the initiation of sunitinib therapy. These outcomes will be evaluated by qualified dermatologists.

#### Secondary Outcomes

The secondary outcomes of Phase I are hematological test abnormalities within the observation period. The secondary outcomes of Phase II are development of grade 2 or higher HFSR within 6 weeks of sunitinib therapy, progression-free survival and time-to-treatment failure of sunitinib therapy, dermatological abnormalities of the palmar or plantar surfaces within the observation period, and development of grade 2 or higher HFSR within 3 weeks after completion of the investigational treatment. HFSR and dermatological abnormalities will be evaluated by qualified dermatologists.

### Safety Endpoints

The safety endpoints are dermatological abnormalities in palmar or plantar surfaces, such as bullous dermatitis, dry skin, erythroderma, pruritus, purpura, rash maculopapular, skin hyperpigmentation, and skin hypopigmentation, as well as the frequency and severity of treatment-emergent adverse events. These adverse events have a cause-and-effect relationship with the investigational preparation, so we will also observe them over the whole treatment period.

### Study Procedure

The study schedule is shown in Table 1. Screening tests will be performed within 1 week of obtaining informed consent and researcher confirmation of each patient’s eligibility. Eligible patients will be enrolled via electronic case report forms (eCRFs).

Baseline data will be corrected beginning on the initial day of investigational cream usage. Patient-specific data (ie, sex, height, weight, concomitant diseases, medical history, prior chemotherapy, etc) and hematological and biochemical test data will be acquired from patients’ electronic medical records as per usual care practice information. The baseline dermatological status of each participant will be determined from the screening test.

Patients will receive sunitinib for 2 weeks, followed by a 1-week interruption; therefore, the therapeutic cycle lasts for 3 weeks. The initial dosage of sunitinib will be 37.5 mg/day. The participants will begin treatment with Amitose DGA-containing cream simultaneously with the start of sunitinib therapy. Plasma concentrations of sunitinib will be measured 10-14 days after the start of sunitinib therapy, as per usual care practice. HFSR will be checked regularly by the hospital urologists during the first 2 weeks of sunitinib therapy; during this period, the patients will remain in hospital.

During week 3 and week 6 outpatient clinical visits, participants will receive dermatological examinations by a dermatologist. This examination will focus on dermatological abnormalities of the palmar or plantar surfaces to assess the safety of the Amitose DGA-containing cream in Phase I. The dermatologist will additionally assess the efficacy of the Amitose DGA-containing cream at these visits during Phases I and II.

### Assessments

#### Hand-Foot Skin Reaction

HFSR grading will be done according to that for palmar-plantar erythrodysesthesia syndrome, as described by the National Cancer Institute CTCAE, version 4.0. The dermatologists will then determine the efficacy of the investigational preparation.

**Table 1 table1:** Study schedule of events.

Study events and measurements	Screening phase	Treatment phase^a^						Posttreatment observation phase
	Within 1 week of obtaining informed consent	Week 1	Week 2	Week 3	Week 4	Week 5	Week 6	Week 9
Sunitinib treatment		✓︎	✓︎		✓︎	✓︎		
Application of Amitose DGA cream		✓︎	✓︎	✓︎	✓︎	✓︎	✓︎	
Informed consent	✓︎							
Patients’ backgrounds	✓							
Hematology^b^ and biochemistry^c^	✓			✓			✓	
Sunitinib plasma concentration			✓					
Subjective symptoms	✓	✓		✓			✓	✓
Objective findings	✓	✓		✓			✓	✓
Dermatological examination	✓			✓			✓	
Adherence confirmation		✓	✓	✓			✓	
Observation of adverse events		✓︎	✓︎	✓︎	✓︎	✓︎	✓︎	✓︎

^a^The weeks listed correspond to the weeks after initiation of sunitinib.

^b^Hematology tests include red blood cell counts, hemoglobin, hematocrit, differential leukocyte counts, and platelet counts.

^c^Biochemistry tests include total protein, serum albumin, aspartate aminotransferase, alanine aminotransferase, alkaline phosphatase, gamma-glutamyl transpeptidase, lactase dehydrogenase, total bilirubin, direct bilirubin, creatine kinase, blood urea nitrogen, serum creatinine, uric acid, and serum concentrations of sodium, potassium, chloride, and calcium.

#### Compliance for Use of Investigational Preparation

Participant compliance will be monitored by the medical staff while the participants are inpatients. Once participants are transitioned to outpatient treatment, we will calculate a compliance ratio for the investigational preparation by determining instances of daily use, based on diaries kept by individual participants.

#### Dermatological Abnormalities

Dermatological abnormalities will be defined as grade 1 or higher dermatological events, including bullous dermatitis, dry skin, erythroderma, pruritus, purpura, rash maculopapular, skin hyperpigmentation, and skin hypopigmentation, as specified by the CTCAE, version 4.0. Dose-limiting toxicities will be defined as grade 2 or higher events. If dose-limiting toxicity is more than 40% and is confirmed to be causally connected to the use of the investigational preparation, the study will be terminated and will not advance to Phase II.

#### Plasma Concentration of Sunitinib

Plasma concentrations of sunitinib will be measured 10-14 days after the start of sunitinib therapy, as per usual care practice; the trough level of total concentration of sunitinib and its metabolite N-desethyl-sunitinib will be measured.

#### Progression to Sunitinib Therapy

Before the introduction of sunitinib, all patients will undergo radiological examinations, including computed tomography (CT) imaging of the brain, chest, and abdomen, or radionuclide bone scans, or both. Typically, tumor measurements are performed using CT every 8-12 weeks after initiating sunitinib therapy. All responses will be assessed by a treating physician based on the Response Evaluation Criteria in Solid Tumors, version 1.1.

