### Discontinuation of Study Subject Participation

Necessary testing will be carried out to assess the efficacy and safety of the Amitose DGA-containing cream if its use is permanently discontinued due to termination of subject participation in the study. Participants can be withdrawn from the study if their consent is withdrawn; if inadequacies are found after enrollment; if sunitinib therapy is determined to be unnecessary because of RCC resolution; or if the patient is unable to continue sunitinib therapy because of disease progression, complications, or adverse events induced by sunitinib or Amitose DGA-containing cream. Participation can be terminated in cases of pregnancy, noncompliance with the use of the investigational preparation (ie, compliance ratio less than 70%), if the study is discontinued, or if other issues emerge that warrant study discontinuation, according to the physician.

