#### Secondary Analysis

Secondary analysis on the efficacy of the investigational preparation throughout the whole observation period will be performed for additional discussion on the primary analysis, but multiplicity will not be adjusted in this analysis. Hypothesis testing will be performed with a two-sided 5% significance level and a two-sided 95% CI.

Logistic regression analysis, setting the development of HFSR as the dependent variable, will be performed by examining independent variables, including patient characteristics, sunitinib dose, and plasma concentrations of sunitinib, with a two-sided significance level of 5% and a two-sided 95% CI. Moreover, progression-free survival and time-to-treatment failure will be determined using the Kaplan-Meier estimate; medians and 95% CIs will be calculated.

We will carry out imputation for missing data by multiple imputation, as appropriate. Primary analyses will be performed by intention-to-treat analysis. Secondary analyses will consider per-protocol set, including participants who completed the treatment according to the scheduled protocol.

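### A single-arm median of progression-free survival or time-to-treatment failure, with no reference value, cannot show what the cream does to sunitinib outcomes

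*Protocol article*

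**What the plan says.** - **Objective.** The last secondary objective (Study Objectives) asks for the cream's effects on the therapeutic results of sunitinib. The Discussion ends with the expectation that the cream may relieve suffering and also improve those results.
- **Endpoints.** Secondary Outcomes lists "progression-free survival and time-to-treatment failure of sunitinib therapy" for Phase II, with no time limit on either.
- **Design.** Study Design: "This is an ongoing Phase I/II, single-center, uncontrolled, single-arm, open-label clinical trial".
- **Analysis.** Secondary Analysis: "progression-free survival and time-to-treatment failure will be determined using the Kaplan-Meier estimate; medians and 95% CIs will be calculated". No test, comparison or reference value is attached to either endpoint.
- **Analysis set.** The same section gives primary analyses to intention-to-treat and directs secondary analyses to a per-protocol set of participants who finished treatment as scheduled.
- **Imaging.** Progression to Sunitinib Therapy: "Typically, tumor measurements are performed using CT every 8-12 weeks after initiating sunitinib therapy".
- **Exposure.** Intervention: the cream is applied "within two treatment cycles (ie, 6 weeks) of sunitinib".
- **Benchmark.** Sample Size Calculation and Primary Analysis give one historical figure for comparison, the institution's 33.3% rate of hand-foot skin reaction (HFSR) of any grade.
- **Withdrawal.** Discontinuation of Study Subject Participation lets participation end for, among other reasons, progression, adverse events that prevent further sunitinib, or cream compliance below 70%.

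**The concern.** The objective is causal: it asks what the cream changes. An answer needs an outcome without the cream, either from a control group or from a stated reference. For HFSR the authors supply a reference. For PFS and time-to-treatment failure they supply none, so the planned medians describe how patients at one hospital fared on sunitinib while also using a cream for six weeks.

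A median that looks long could be taken as oncological benefit of a skin cream, and one that looks short as harm. Neither reading would have support, yet the objective and the closing sentence of the Discussion invite the first.

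The analysis set adds a second problem. For endpoints whose events are progression or stopping sunitinib, a set limited to people who completed treatment removes those who failed early.

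**Working it through.** **1. What the article does for HFSR.** Inputs from Sample Size Calculation: 33.3% any grade, 2.2% grade 3, 75% of grade 1-2 prevented, alpha 0.05, power 80%, no continuity correction.

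- Expected rate: 0.25 × (0.333 − 0.022) + 0.022 = 0.0998, the stated 10%.
- Two-sided one-sample formula: n = [(1.960 × √(0.333 × 0.667) + 0.842 × √(0.10 × 0.90)) / 0.233]² = 25.5, against 25 stated.

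This essentially reproduces. It also shows that the single-arm comparison works only because p0 = 33.3% is supplied.

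**2. The same elements for the therapeutic endpoints.**

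| Element | HFSR | PFS, time-to-treatment failure |
|---|---|---|
| Reference value | 33.3% | none |
| Hypothesis | one-sample test at 5% | none |
| Concurrent control | none | none |
| Planned output | test of one proportion | median and 95% CI |

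An effect is a difference or ratio between two quantities. In the right-hand column only one exists. There is no contrast within the trial either, because every participant is assigned the cream.

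**3. Does longer follow-up help?** The documents give no PFS median, so 6 to 20 months is assumed, with exponential times. Further assumptions:

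- The 21 recruits at publication took 24 months (August 2017 to August 2019), or 0.875 a month, so 30 take 30 / 0.875 = 34.3 months, evenly spaced.
- Follow-up closes in January 2021 (month 41) or December 2021 (month 52).

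Expected events = Σ(1 − 0.5^(f/m)) over 30 participants with follow-up f and median m, both in months:

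| Assumed median | To January 2021 | To December 2021 |
|---|---|---|
| 6 months | 26.4 | 29.0 |
| 12 months | 21.0 | 25.3 |
| 20 months | 16.0 | 20.5 |

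The 95% CI for an exponential median with d events is about the estimate × exp(±1.96/√d):

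- d = 16: exp(±0.490), factors 0.61 to 1.63.
- d = 29: exp(±0.364), factors 0.69 to 1.44.

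An estimate of 12 months from 21 events would run from 12 × 0.65 = 7.8 to 12 × 1.53 = 18.4 months. Such a median is estimable but wide, and it still has nothing to be compared with.

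**4. What restriction to completers does.** Take completion as six weeks on treatment: 6 / 4.348 weeks per month = 1.38 months. Assume that everyone who fails before then is left out. Under an exponential distribution the median among those remaining, counted from the start of sunitinib, is m + 1.38:

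| Assumed median | Left out: 30 × (1 − 0.5^(1.38/m)) | Median in completers |
|---|---|---|
| 6 months | 4.4 | 7.4 months (+23%) |
| 12 months | 2.3 | 13.4 months (+11%) |
| 20 months | 1.4 | 21.4 months (+7%) |

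This bears most directly on time-to-treatment failure. For PFS fewer early events would be recorded, because the usual first CT falls at 8 to 12 weeks, but the direction is the same.

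**The case against.** **The analysis is already descriptive.** Secondary Analysis plans no test and does not say that the medians demonstrate an effect. The single-arm design is declared, and the authors call the evidence preliminary and of limited application. All of this stands, and it is why rewording is enough. It does not remove the mismatch, because the objective still asks for an effect and the Discussion still anticipates better outcomes.

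**The institution's earlier cohort could serve as a reference.** The article takes only HFSR rates from it, and the Discussion says its exclusion criteria differed from those of this trial.

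**The per-protocol sentence is loose.** It may mean an additional analysis, and it does not say whether the treatment completed is the cream or sunitinib. The upward bias therefore depends on reading it as written.

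**Stronger readings that the documents do not support.**

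- A reader might infer from Table 1, whose last column ("Posttreatment observation phase") is week 9 and which has no imaging row, that PFS observation stops there and the median cannot be reached. The article does not say so. Week 9 is six weeks of cream plus the three weeks needed for another endpoint, "development of grade 2 or higher HFSR within 3 weeks after completion of the investigational treatment". PFS carries no time limit, CT is described as recurring usual care, and completion is expected in 2021. Table 1 simply does not cover tumour follow-up. A cut-off and censoring rules may sit in the full protocol.
- A reader might infer that withdrawal "if sunitinib therapy is determined to be unnecessary because of RCC resolution" censors the best responders. That section states no censoring rule and does not say that outcome collection ends at withdrawal.

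**Conclusion.** The point holds. The objective is causal, the design has one arm, no reference PFS or time-to-treatment failure is given, and the analysis yields only medians with intervals. These endpoints therefore cannot show an effect of the cream at any length of follow-up. This conclusion needs no numerical assumption.

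The figures only illustrate size. About 16 to 29 events of 30 by 2021 and an interval of roughly 0.6 to 1.6 times the median rest on assumed medians, exponential times and even accrual. The completer shift of about 1.4 months also assumes that all failures within six weeks are left out.

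The point touches a secondary objective. It does not affect the primary outcomes, the sample size or the Phase I stopping rule. It is worth changing because it decides what the trial may conclude about cancer outcomes.

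**What to change.** 1. Reword the secondary objective to: *describe PFS and time-to-treatment failure of sunitinib in participants using the cream*. Remove the expectation of improved therapeutic outcomes from the Discussion and from later reports.
2. State that both endpoints are estimated in all enrolled participants from usual-care records, and that follow-up for them continues after the cream or the study visits stop. Do not use the completer set for these two endpoints.
3. Note beside Table 1 that it does not cover tumour follow-up.

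The cost is protocol wording plus abstraction of scans and treatment dates already recorded in usual care. The downside is that the therapeutic-outcome result becomes descriptive only, which is all this design can deliver.
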